#### Serum collection

Approximately 30 mL of blood will be taken from each participant (BD Vacutainer Tube SST Advance). Serum will be extracted and stored at −80°C in compliance with The Human Tissue Act 2004. Levels of proteins associated with inflammation, such as pro-inflammatory cytokines, will be measured using electrochemiluminescence. All serum samples will be collected and stored in accordance with the Human Tissue Act.

#### Sub study: skin biopsies

For the substudy, two 3 mm diameter skin samples will be taken from the ventrolateral aspect of the proximal phalanx of the index finger on the more affected side and 10 cm above the contralateral lateral malleolus under sterile conditions using local anaesthesia (1% lidocaine, 1.0–2.0 mL). We will fix the biopsies in a periodate-lysine-paraformaldehyde solution for 30 min followed by washing samples in 0.1 M phosphate buffer. The tissue will be embedded in an OCT compound and stored at −80°C. Sections of 50 μm will be cut and immunohistochemistry will be performed to visualise cutaneous nerve fibres (eg, with protein gene product 9.5). A single, blinded assessor will evaluate the integrity of intraepidermal and dermal nerve fibres, as previously detailed.^44–46^ In brief, intraepidermal nerve fibre density will be counted through the microscope from three samples per patient with the average expressed as fibres per mm epidermis.^46^ Dermal innervation will be established by counting the number of dermal nerve bundles per mm^2^ dermis that include at least five axons.^47^ All skin samples will be collected and stored in accordance with the human tissue act.

#### Follow-up

All participants will be asked to complete the questionnaires and answer a self-rated global recovery question 6 months after their injury. Twenty five participants who have recovered and 25 who have not recovered will undergo the full protocol. To promote participant retention, a newsletter will be sent to participants to keep them up to date about the study, and a small payment will be given to those who return their completed questionnaires at 6 months or attend their follow-up appointment.

### Data storage and analysis

Data and samples will be anonymously coded, and stored on a secure web platform (REDCap (Research Electronic Data Capture), Vanderbilt University, Nashville, USA) and university freezers, respectively. Anonymised imaging data will be stored in DICOM and NIfTI formats on secure university servers. Participants will be identified by a unique study specific code. All data and sample analyses will be blinded to participant group and time point.

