**Trial registration number:**

NCT04940923.

Strengths and limitations of this studyThis study will evaluate the contribution of peripheral nerve inflammation to whiplash-associated disorder grade 2 and its role in prognosis.The design will enable us to understand if simple clinical tests can be used to identify nerve inflammation.One potential limitation of a two-site study can be variation in data collection between sites, although regular meetings and site visits have been put in place to minimise this.The use of different scanners could result in non-homogenous data sets; however, identical scanner types are being used, which should reduce the impact of this potential issue.It is not possible to blind the examiner to the status of patients versus healthy control participants, which may influence digital nerve palpation; therefore, care will be taken to ensure similar pressures are applied to both groups where possible.

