### Study design

This is a prospective cohort study at two centres. A total of 115 participants will be recruited following a whiplash injury within 1 month of their original injury. We will also recruit 34 healthy proportionally age-matched and gender-matched control participants. People with acute WAD2 and healthy control participants will attend a baseline appointment. In addition to MRI, a detailed musculoskeletal assessment will be performed, as well as tests of nerve trunk mechanical sensitivity and quantitative sensory testing (QST). A blood sample will be taken and analysed for levels of inflammatory markers. Participants will also be asked to complete a series of validated questionnaires to assess neuropathic symptoms, functional deficits, quality of life and psychological factors. For the substudy, skin biopsies from the index finger and ankle will also be taken. At 6 months, the Neck Disability Index and a self-rated global recovery question will be used to determine recovery. A sequential sample of patients will be invited to attend a follow-up appointment during which the same detailed assessments will be repeated (figure 1).

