#### Nerve mechanical sensitivity testing

Test of nerve trunk mechanical sensitivity of the brachial plexus, median and ulnar nerves will be performed bilaterally. The ULNT1 (median nerve bias^39^), will be performed as per standard sequence^40^ using 90° abduction and lateral rotation of the shoulder, elbow supination, wrist and finger extension followed by elbow extension. The ULNT3 (ulnar nerve bias^40^) will be performed using shoulder abduction, forearm pronation, wrist and finger extension followed by elbow flexion. The ULNT1 and ULNT3 tests are considered ‘positive’ when there is reproduction of participant’s symptoms and these are changed with the addition of a structural differentiation manoeuvre^39^ (table 1). For the ULNT1, elbow range of flexion at the point of symptom onset will be measured using a digital inclinometer (Trend, DLB Swansea, UK). Mechanosensitivity to pressure will be established by both response to digital pressure and using an algometer (tip size=1 cm^2^, Wagner, USA). The algometer will be used over the ulnar nerve at the proximal cubital tunnel and the carpal tunnel bilaterally. Participants will be asked to inform the researcher at the point where the pressure applied over the nerve changes to pain. Measurements will be taken three times at each site and averages used for analysis. Other sites (bilaterally at brachial plexus in the supraclavicular area, median nerve at the proximal wrist crease, ulnar nerve at Guyon’s canal) will be palpated digitally and graded according to symptom response (see table 1). Phalen’s and Tinel’s test will be performed bilaterally at the wrists.^41^

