### Statistical analysis

Data will be exported to Stata (V.17, StataCorp, Texas, USA) for analysis. The distribution of the data will be checked for normality, and parametric, or non-parametric methods will be used as appropriate. Participants’ characteristics will be described at all time points.

For objective 1, regression analysis, or non-parametric tests, will be used as appropriate to identify differences in MRI parameters (T2-weighted STIR 4 nerve roots per side, nerve morphology and DTI parameters) and clinical tests (eg, neuropathic pain scores, tests of nerve mechanosensitivity, QST and serum inflammatory markers) between participants with acute WAD2 and age/gender-matched controls. Regression analysis will be used to assess associations with age and height.

For objective 2, recovery of participants with WAD2 will be determined at 6 months with the Neck Disability Index and a global recovery question. The analysis will be conducted with three models using different predictors measured in the acute stage: (a) MRI parameters of neuroinflammation, (b) clinical parameters that reflect neuroinflammation and (c) the addition of MRI to clinical parameters to determine whether this improves predictive strength. The dependence between MRI and clinical assessments will be investigated and composite measures added to the model. In addition, a linear regression will be performed of Neck Disability Index scores on measures of neuroinflammation.

For objective 3, mixed effects modelling will be used to compare MRI and clinical measures between recovered and non-recovered participants with WAD2 over time.

For objective 4, multivariable regression will be used to investigate the relationship of each MRI variable with the clinical parameters of neuroinflammation. In addition, a regression analysis will be performed between clinical measures of neuroinflammation and MRI parameters.

For the substudy, independent t-tests or non-parametric alternatives will be used to compare dermal and intraepidermal nerve fibre density in skin biopsies in patients in the acute phase after whiplash injury with healthy controls. Separate regression models will be used to investigate whether changes in nerve fibre density in the acute stage predict pain persistence at 6 months.

Data reduction techniques (eg, principal components analysis) may be used prior to regression modelling.

Missing data will be managed with multiple imputation strategies.

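### Objective 3 compares examiner-graded clinical tests between recovered and non-recovered participants, but nothing in the article keeps the 6-month examiner unaware of recovery status

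*Protocol article*

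**What the plan says.** **Who returns.** The Follow-up section states: "Twenty five participants who have recovered and 25 who have not recovered will undergo the full protocol". The sample size section repeats the 25/25 split for objective 3. Study design describes the visit thus: "A sequential sample of patients will be invited to attend a follow-up appointment during which the same detailed assessments will be repeated".

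**How the groups are formed.** Under Statistical analysis, "recovery of participants with WAD2 will be determined at 6 months with the Neck Disability Index and a global recovery question".

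**What is repeated.** The nerve mechanical sensitivity section says that several nerve sites "will be palpated digitally and graded according to symptom response". It also says: "The ULNT1 and ULNT3 tests are considered ‘positive’ when there is reproduction of participant’s symptoms", with a further condition that the symptoms change on structural differentiation. Phalen's and Tinel's tests, algometry and quantitative sensory testing (QST) belong to the same examination.

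**What is compared.** For objective 3, "mixed effects modelling will be used to compare MRI and clinical measures between recovered and non-recovered participants with WAD2 over time".

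**What is blinded.** Data storage and analysis says: "All data and sample analyses will be blinded to participant group and time point". Image analysis says that MRI data are coded and analysed blind, and the skin biopsy section provides for one blinded assessor. The only statement about the examiner is in the strengths and limitations list: "It is not possible to blind the examiner to the status of patients versus healthy control participants, which may influence digital nerve palpation". The safeguard offered there is care to apply similar pressure in both groups.

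**The concern.** Blinding the analysis cannot remove a bias that entered when the measurement was made. In digital palpation the examiner chooses the pressure and records the grade. In the neurodynamic tests the examiner moves the limb and decides whether the response counts as positive. The article accepts that knowing a participant's status may influence palpation, but applies this only to patients versus controls, where it considers masking impossible.

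The recovered versus non-recovered contrast is different. That status rests on questionnaire answers, which can be withheld from the examiner. The contrast also carries the clinical part of objective 3. If the examiner knows that a person was invited as non-recovered, a difference in nerve mechanosensitivity at 6 months could partly reflect expectation rather than the nerve.

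**Working it through.** **Step 1: follow the status information through the article.**

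| Stage | What the article provides | Examiner kept unaware of recovery status? |
|---|---|---|
| Baseline examination | Within 4 weeks of injury; recovery not yet determined | Not needed: status does not exist |
| Classification at 6 months | Neck Disability Index and global recovery question | Not stated who sees the answers |
| Invitation | 25 recovered and 25 non-recovered | Not stated who fills the groups |
| 6-month examination | Same assessments repeated | No provision |
| MRI, serum and biopsy readings | Blinded | Protected |
| Data analysis | Blinded to group and time point | Protected, but after the grades are recorded |

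The section on standardisation across sites does not fill the gap. It covers piloting of procedures, inter-rater reliability of the inclinometer range of motion, and comparison of healthy controls between sites.

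**Step 2: where the bias would appear.** Write the recorded score as true score plus examiner effect. Knowledge of recovery status cannot affect the baseline score. If it adds b to the non-recovered minus recovered difference at 6 months, the expected group-by-time contrast is the true contrast plus b. Baseline adjustment cannot remove b, because b is absent at baseline.

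**Step 3: reproduce the plan's own figure.** Inputs from the sample size section: effect size 0.9, correlation 0.5, 95% power, 5% significance (taken as two-sided), analysis of covariance.

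- n per group = 2 × (1.960 + 1.645)² × (1 − 0.5²) / 0.9² = 2 × 12.995 × 0.75 / 0.81 = 24.1, rounded up to 25.
- Standard error at 25 per group = √0.75 × √(2/25) = 0.245 SD.
- Power at 25 per group = 95.7% (normal) or 94.9% (noncentral t).

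The stated figure reproduces and is not in dispute.

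**Step 4: sensitivity to an assumed b.** The article gives no value for b. With no true difference and the standard error above, the two-sided 5% test rejects as follows (normal approximation).

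| Assumed b (SD) | b / 0.245 | Rejection rate |
|---|---|---|
| 0 | 0 | 5.0% |
| 0.1 | 0.41 | 6.9% |
| 0.2 | 0.82 | 12.9% |
| 0.3 | 1.22 | 23.2% |
| 0.5 | 2.04 | 53.2% |

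This shows only how a comparison of this size would respond to a shift. It does not estimate the shift. The 0.9 effect is not tied to any clinical test, palpation is a short ordinal grade, and the neurodynamic tests are positive or negative, so an SD scale fits them poorly.

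**The case against.** **The article is condensed.** It refers to a protocol version that is not shown, and that document may contain an examiner-masking rule. This limits the point but does not remove it. The article sets out its blinding in several places and discusses the examiner explicitly, yet for one contrast only. Followed as written, it leaves the follow-up examiner unmasked.

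**The article does not show that the examiner knows the status.** A reader might infer that the people who fill the 25/25 groups also do the examinations, or that the questionnaires are returned before the visit. Neither is stated. The quotas make classification before invitation plausible, but no order and no division of roles is given. The supportable statement is that nothing separates the roles.

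**Masking cannot be complete.** This stands. Neurodynamic positivity depends on reproducing the participant's own symptoms, palpation grades record the participant's response, and participants may disclose how they are. Participants also know whether they have recovered, and that source of bias remains whatever the examiner knows. The bias is reducible, so it would be too strong to call it avoidable.

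**Exposure is limited.** This also stands. MRI, serum and biopsy readings are blinded. Algometry and inclinometer measurements give instrument readings, and algometry is averaged over three measurements, so they are less exposed than digital grades.

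**The blinding sentence is accurate.** A reader might take it as a claim about the whole study, but it speaks of analyses. It needs no narrowing, and limiting it to imaging and laboratory work would withdraw a commitment to blinded data analysis.

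**Conclusion.** The point holds for objective 3's examiner-dependent clinical tests: digital palpation grades, the neurodynamic tests, Phalen's and Tinel's tests and, to a lesser extent, algometry and QST. Attendance at 6 months is selected by recovery status, and no part of the article keeps the examiner unaware of it. Expectation arising from that knowledge can act only at follow-up and could appear as a group-by-time difference.

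Its size cannot be estimated from the article. A reader might take the rejection rates in the working as the expected inflation of false positives, but they rest wholly on assumed shifts. The MRI comparison in objective 3 and the serum and biopsy readings are not affected. The conclusion assumes that the full protocol contains no masking rule that the article leaves out. The change is a worthwhile, inexpensive improvement to a secondary part of objective 3; the design and its sample size stand.

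**What to change.** 1. Have an existing team member who does not examine the participant classify recovery and issue the invitation.
2. Restrict the examiner's REDCap view so that the 6-month Neck Disability Index and global recovery answers are hidden until the examination is recorded.
3. At the 6-month visit, do the graded tests before symptom history, the pain scale and questionnaires. Use the test side recorded at baseline; QST is otherwise done on the most symptomatic side, which would require asking first.
4. Where masking is not achieved, including at visits already completed, list this as a limitation of objective 3's clinical comparison.
5. Leave the commitment to blinded data analysis unchanged.

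The cost is a reordered visit, a restricted database view and some coordination over who classifies and who examines. The article gives no staffing, so it should be confirmed that an existing team member can take this on. The sample size does not change. The downside is that masking will be partial, for the reasons given under the objection.

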#### Image analysis

MRI data will be coded and analysed blindly. T2-weighted signal intensity will be analysed using MATLAB (Mathworks, Natick, USA, release 2022a). Briefly, regions of interest within the brachial plexus and the median nerve will be identified, and a binary mask created to allow for background subtraction. Following background subtraction, the mean pixel grayscale value for each nerve segment will be determined and normalised to a region of adjacent tissue.

Brachial plexus DTI data will be de-noised using a self-supervised machine learning approach^48^ implemented in Dipy.^49^ Wrist DTI data will be denoised using a method based on random matrix theory,^50^ implemented in MRtrix. Subsequently, they will be corrected for susceptibility and eddy current distortions using a combination of TopUp and Eddy (part of the FMRIB’s software library). DTI fitting will be performed for both kinds of data using tools from the FMRIB’s software library to create fractional anisotropy, mean diffusivity and other parametric maps.^26^ Mean DTI parameters will be determined within regions of interest.

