Magnetic resonance (MR) neurography has gained increasing interest in the diagnosis of peripheral nerve pathology.^21–23^ An increased signal intensity on T2-weighted sequences is considered an imaging correlate of the intraneural oedema associated with peripheral neuroinflammation. Accordingly, T2-weighted signal is increased in animal models of neuroinflammation,^24 25^ and correlates positively with histological findings of inflammation.^25^ Using T2-weighted MR neurography in a group of patients with chronic WAD2, we have identified increased signal intensity in the cervical nerve roots and the median nerve at the carpal tunnel, indicative of peripheral neuroinflammation.^9^ In addition to T2-weighted MR neurography, diffusion tensor imaging (DTI) has recently been employed to examine the microstructural integrity of peripheral nerves.^26 27^ DTI evaluates the diffusivity of water molecules within nerves, which can provide information on the integrity of axons and myelin sheaths,^28 29^ as well as intraneural oedema.^30^

In addition to neuroinflammation and functional changes to the nervous system, there is also some evidence for the presence of structural nerve pathology in patients with WAD2. This is apparent by a decreased intraepidermal nerve fibre density in the index finger in patients with chronic WAD2.^14^ It currently remains unknown whether such small fibre degeneration is already apparent in the early stages after injury and whether it predicts outcome.

The main aim of this study is to establish the contribution of peripheral nerve pathology to WAD2 and its role in prognosis. Our primary focus is on peripheral neuroinflammation, which we will evaluate using a detailed examination, including MRI of the brachial plexus and distal nerve trunks, blood markers and clinical tests of nerve trunk mechanical sensitivity. Additionally, recruited participants will be invited to participate in a substudy that will use skin biopsies to establish the contribution of cutaneous nerve fibre pathology to WAD2. Our results will advance our understanding of the pathology underlying WAD2 and may identify factors that predict the development of persistent symptoms.

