## Methods and analysis

### Objectives

The first objective of this study is to determine the presence of peripheral neuroinflammation during the acute stage following a WAD2 injury. This objective will use MRI to assess the extent of peripheral neuroinflammation and nerve microstructure in a cross-section of patients within 4 weeks of injury and healthy controls. The second objective will determine whether the presence of peripheral neuroinflammation in the acute stage can predict patient recovery status at 6 months. The third objective will determine the course of peripheral neuroinflammation from the acute to chronic stages of a WAD2 injury. For this objective, we will examine changes in MRI measures and clinical tests from baseline to 6 months in both recovered and non-recovered patients. The fourth objective will determine whether low-cost clinical tests can serve as markers to detect neuroinflammation as determined on MRI. The objective of the substudy is to determine whether the structural integrity of cutaneous nerve fibres is altered in the acute stage following a WAD2 injury, and whether it contributes to the progression to chronicity.

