### Participant recruitment

Patients aged 18–60 that meet the Quebec Task Force Classification of WAD2 will be recruited within 4 weeks of injury. Participants will be recruited from emergency departments and minor injury units in Surrey, Sussex, Kent and Oxfordshire, directly by clinicians, and following weekly hospital database searches using defined search terms (eg, motor vehicle collision, muscle injury: neck, bruise/contusion/abrasion: neck, sprain/ligament injury: cervical spine). Potential participants will be contacted in person, or by phone, and asked for permission for their details to be passed on to the study team, and/or sent the study details. In addition, posters will be displayed in departments with study contact details. Healthy age-matched and gender-matched control participants will be recruited through departmental emailing lists (Universities of Sussex and Oxford as well as local hospitals), social media and flyers on public notice boards. Potential participants will be screened for suitability via telephone and also be invited to take part in the substudy. Eligible individuals will be sent a participant information sheet and questionnaires to complete (please see table 1 and questionnaire section below) and will be invited to attend a baseline appointment at either Brighton and Sussex Medical School, University of Sussex, Falmer or the Nuffield Department of Clinical Neurosciences, University of Oxford.

**Table 1 T1:** Summary of self-reported and physical assessments

Test	Description	Type of tool/assessment	Participants
Demographics	Age, gender, height/weight.	Self-reported.	HC and whiplash
Injury details	Impact, anticipation.	Self-reported.	Whiplash
Medication details	Specific to WAD symptoms.	Self-reported.	Whiplash
Symptom history	Description of pain or symptoms.	Self-reported.	Whiplash
Pain level	Current pain severity.	Visual Analogue Scale.	Whiplash
Management	Any investigations/treatment.	Self-reported.	Whiplash
Type of pain	Neuropathic pain.	painDETECT Questionnaire.	Whiplash
Disability	Neck disability.	Neck Disability Index.	Whiplash
Psychological factors	Post-traumatic stress. Pain catastrophising. Depression, anxiety and stress. Quality of life.	PTSD-8. Pain Catastrophising Scale. DASS 42. EQ-5D-5L.	Whiplash

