### Sample size calculation

Mean nerve signal intensity ratio data from our previous cross-sectional study of 13 controls and 9 participants with chronic WAD2 were analysed using a linear mixed model.^9^ The observed difference in means between controls and WAD2 participants was 0.0600 (SE=0.0315) for the C5–C8 roots of the brachial plexus, which was statistically significant; age was not a statistically significant covariate. The intraclass correlation coefficient of the nerve signal ratio was estimated to be 0.45. Assuming that there are eight assessments per participant (two sides × four roots), a SD of 0.1, intraclass correlation coefficient of 0.45 and a ratio of 3 participants with whiplash to one healthy control, the study would require 48 participants with whiplash and 16 controls to detect an effect estimate of 0.06 for the mean nerve signal intensity difference (80% power, 5% significance). Since in the acute stage it is estimated that only 50% of the participants with whiplash will develop chronicity,^51^ we will need to image 96 participants with whiplash and 32 controls for objective 1 (difference in neuroinflammation in the acute stage). Based on ~48 participants who have not recovered at 6 months, we would be able to fit a logistic regression model with 5–10 predictor variables for objective 2 (predictive factors of chronicity).

For objective 3 (development of neuroinflammation over time), we will ask 25 participants who have recovered and 25 participants who have not recovered to return at 6 months, which will enable an effect size of 0.9 to be detected using analysis of covariance, with 95% power for 5% significance. This value assumes that the correlation between the acute and chronic measurements is 0.5.

For objective 4 (validity of low cost tests of neuroinflammation), with nine independent variables, a rule of thumb for a multiple linear regression (ie, 10 participants per additional variable) implies that data from 90 participants with whiplash should be adequate to explore this.^52^

For the substudy, 68 participants with whiplash and 34 healthy controls (80% power, 5% significance, 0.53 effect size, one-tailed test) would allow the detection of a 20% smaller difference in intraepidermal nerve fibre density in the acute stage compared with healthy controls based on our previous cohort of patients with chronic WAD2.^53^

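### The cervical-root T2 ratio uses adjacent neck tissue as its denominator, which may itself be brighter soon after whiplash; a second reference region should be pre-specified as a sensitivity analysis

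*Protocol article*

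**What the plan says.** Image analysis gives a short account of the T2 measure. Nerve regions are masked, background is subtracted, and "the mean pixel grayscale value for each nerve segment will be determined and normalised to a region of adjacent tissue". The reference tissue is not named.

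Statistical analysis lists the MRI parameters compared between patients and controls for objective 1 as "T2-weighted STIR 4 nerve roots per side, nerve morphology and DTI parameters". The sample size for that objective rests on the root signal ratio, with a difference of 0.06 taken from "our previous cross-sectional study of 13 controls and 9 participants with chronic WAD2".

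The Objectives section places the first scan "in a cross-section of patients within 4 weeks of injury and healthy controls". Participant recruitment gives examples of database search terms, among them motor vehicle collision and "muscle injury: neck, bruise/contusion/abrasion: neck, sprain/ligament injury: cervical spine". The Introduction explains why T2 signal is used: "An increased signal intensity on T2-weighted sequences is considered an imaging correlate of the intraneural oedema associated with peripheral neuroinflammation".

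**The concern.** A ratio measures the nerve only if its denominator is unrelated to what is being compared. The article reads brighter T2 signal as a sign of oedema in nerve, and the same reading would apply to oedema in neighbouring soft tissue. Tissue beside the cervical roots lies in the injured region in patients. Controls must have no history of whiplash and no recent treatment for neck, thoracic spine or upper limb pain. Any acute soft-tissue signal in the denominator would therefore tend to follow group at baseline, and visit at follow-up.

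Two conclusions are at stake:

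- **Objective 1:** a null root result could mean no nerve signal increase, or a nerve increase offset by a brighter reference.
- **Objective 3:** a rising root ratio between baseline and 6 months could mean developing neuroinflammation, or simply healing soft tissue. A true fall in nerve signal could be masked in the same way.

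A larger sample would not remove a bias of this kind.

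**Working it through.** **Inputs from the article (Sample size calculation):** difference 0.06, SD 0.1, intraclass correlation 0.45, eight assessments per participant, 3:1 ratio, 80% power, 5% significance, then 96 patients and 32 controls for objective 1.

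**Inputs not in the article, so assumed:** the control mean ratio R, and the relative rise x in reference-tissue signal in acute patients.

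**Step 1: reproduce the plan's figure.** The SD of a participant's eight-root mean is 0.1 × √[(1 + 7 × 0.45)/8] = 0.0720. Controls needed, two-sided: (4/3) × [0.0720 × (1.960 + 0.842)/0.06]² = 15.08, so 16 controls and 48 patients. This matches the article; the sample-size arithmetic is not in question here.

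**Step 2: effect of a brighter denominator in patients.** With a true patient ratio of R + 0.06, the observed difference is

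d = (R + 0.06)/(1 + x) − R.

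It is zero when x = 0.06/R, which is 20% at R = 0.3, 12% at R = 0.5, 6% at R = 1 and 3% at R = 2. Example: at R = 1 and x = 5%, d = 1.06/1.05 − 1 = 0.0095.

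**Step 3: power at 96 and 32.** The standard error is 0.0720 × √(1/32 + 1/96) = 0.0147, and power is Φ(d/0.0147 − 1.96). This takes the whole patient group to carry the 0.06 and leaves the SD unchanged. With x = 0, power is 98%.

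| Assumed R | x = 2%: d (power) | x = 5%: d (power) | x = 10%: d (power) |
|---|---|---|---|
| 0.3 | 0.053 (95%) | 0.043 (83%) | 0.027 (46%) |
| 0.5 | 0.049 (92%) | 0.033 (62%) | 0.009 (9%) |
| 1.0 | 0.039 (76%) | 0.010 (just under 10%) | −0.036 (about 0) |
| 2.0 | 0.020 (27%) | −0.038 (about 0) | −0.127 (about 0) |

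**Step 4: change over time.** If the nerve does not change and the reference returns to normal by 6 months, the ratio rises by R − R/(1 + x) = Rx/(1 + x). At x = 5% this is 0.024, 0.048 or 0.095 for R = 0.5, 1 or 2.

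**Step 5: recovered versus non-recovered.** With the same R in both groups and an unchanged nerve, the difference between groups in this spurious change is R × [x₁/(1 + x₁) − x₂/(1 + x₂)], where x₁ and x₂ are the two groups' baseline reference rises. It is zero when x₁ = x₂. The contrast is biased only if reference-tissue signal, or its healing, differs between the groups.

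**Step 6: existing safeguards.** Blinded analysis, the same scanner model at both sites and site adjustment using healthy controls deal with observer and site differences. None corrects a denominator that differs between patients and controls for biological reasons.

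**The case against.** **The premise is not shown.** The article does not report that tissue beside the roots is oedematous in acute WAD2. The search terms are administrative examples, and referral by clinicians and posters are other routes into the study. Scans may take place up to four weeks after injury, and nothing says how much oedema remains by then. This stands: the documents support a vulnerability, not a demonstrated bias.

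**The description is abbreviated.** A fuller imaging document might name a safe reference or a rule to avoid abnormal signal. That is fair, and the unnamed tissue is not the point made here. The point concerns the stated choice of adjacent tissue, which for the cervical roots means tissue in the neck.

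**The alarming figures need R near or above 1.** This also stands. At R = 0.5 with a 2% rise, power is still 92%.

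**Stronger readings that a reader might infer.** The documents do not support these:

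- *Objective 1 as a whole is biased.* It also uses diffusion and morphology measures. The diffusion parameters are not normalised to adjacent tissue, and for the wrist T2 ratio the adjacent tissue is remote from the neck injury.
- *The objective 3 group comparison is biased.* Step 5 shows that this needs differential healing, for which there is no evidence either way.
- *Prediction of recovery (objective 2) and validation of clinical tests (objective 4) are distorted.* That needs a further link between injury severity and reference signal, which the article does not document.
- *The remote reference should replace the adjacent one if the two differ.* Such a switch would choose the outcome from the data. Coil-sensitivity variation alone could trigger it.

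**Conclusion.** The point holds for the brachial plexus (C5–C8) T2 STIR ratio only. If neck soft tissue within four weeks of injury has raised T2 signal, the ratio is lowered in patients relative to controls in objective 1, and the within-patient time course in objective 3 drifts upwards as the tissue heals. The direction follows from the algebra of a ratio. The size cannot be established from the article; the cancellation thresholds and power figures above illustrate sensitivity over assumed values of R and x.

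The pilot does not settle the matter, because its patients had chronic WAD2. The article also does not say what denominator the pilot used. The check is a cheap improvement worth making, because it decides whether a null or changing root ratio can be interpreted. It does not show that the planned measure is invalid.

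**What to change.** 1. Keep the adjacent-tissue ratio as the main T2 measure.
2. On the same brachial plexus images, pre-specify one further reference region, away from the injured neck soft tissue.
3. Compare the adjacent-to-remote reference signal ratio between patients and controls at baseline, and between visits in patients who are rescanned.
4. Report the root T2 results for objectives 1 and 3 again with the remote reference, labelled as a sensitivity analysis.
5. State in advance that, where the two disagree, the root T2 finding, positive or null, will be described as depending on the reference tissue. The main outcome is not switched on the basis of the data.

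The cost is one extra region of interest per existing scan and some analysis wording. At most this is 115 + 34 baseline scans plus 50 at follow-up, 199 in all; no new scans are needed. The downside is that a remote reference is more exposed to coil-sensitivity variation and so is noisier. The stated SD of 0.1 and intraclass correlation of 0.45 are not known to hold for it, so the sensitivity analysis may have less power than the main one, and a non-significant result there should not by itself overturn the main finding.
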